### Primary and secondary outcome measures

The primary and secondary outcome measures are shown in Table 2. We have a number of secondary outcomes as PDUs are understood by trusts to have wide-ranging effects on the crisis care pathway, and this approach allows each of these claims to be investigated. In Table 2, we also specify the denominator used to obtain the rate. A number of different methods have been used to calculate hospital catchment populations (HCPs) in England [39]. Here we will use the proportionate flow methods used by Public Health England (PHE) [40, 41].

**Table 2 Tab2:** Outcome measures

**Primary outcome measures: Synthetic Control (ITS) Study**	
Rate of admissions to mental health trust adult inpatient wards per 1000 trust catchment population	Rate of ED psychiatric presentations per 1000 trust catchment population)
**Primary outcome measures: ITS Study**	
Rate of informal admissions to mental health trust adult inpatient wards per 1000 trust catchment population	Rate of ED psychiatric presentations per 1000 trust catchment population)
**Secondary outcome measures (both studies)**	
**Mental health trust**	**Acute trust**
Rate of inpatient admissions per 1000 trust catchment population	Proportion of 4-h psychiatric ED breaches (denominator psychiatric ED presentations)
Proportion of 0–5 day inpatient admissions (denominator total inpatient admissions)	Average length of psychiatric ED wait
Average length of inpatient stay (bed days)	Proportion of psychiatric ED 12 h trolley waits (denominator psychiatric ED presentations)
Proportion of compulsory admissions (denominator total admissions)	Proportion of psychiatric ED admissions admitted to an acute bed (denominator psychiatric ED presentations)
Proportion of psychiatric liaison episodes at the ED (denominator psychiatric ED presentations)	Proportion of psychiatric ED arrivals by ambulance or police (denominator psychiatric ED presentations)
**ITS only outcomes:**	
Daily mean occupied bed days (denominator size of trust catchment population)	
Proportion of out of area admissions (from the site MH trust to other MH trust or private provider) (denominator total inpatient admissions)	

An additional analysis for all mental health trust outcomes will be conducted considering only people with discharge from psychiatric inpatient services in the preceding 24 months. In a similar manner, additional analyses of the ED psychiatric presentations will be administered considering only people with a previous ED visit in the last 24 months. This is to ensure that we can estimate the effect of introducing PDU on services with respect to those populations most likely to be repeat users of mental health inpatient care and the ED, respectively.

#### Service mapping

We will map the PDUs in England to identify suitable trusts to be used as controls in the synthetic control analysis. We want to ensure that control trusts do not also have PDUs as this will dilute our ability to detect impacts in the treated trusts. Freedom of information (FOI) requests will be sent to all mental health trusts in England to identify the prevalence of PDUs in England. We will use trust websites to generate a contact list and send them the FOI request in the form of an electronic survey.

We will identify the scope of PDUs, the provision of care offered and variation in unit configuration to identify variations in service provision and aid dissemination of the results of the study. In addition, we will obtain information from each trust about alternative assessment and crisis care provision, including assessment wards; community-based assessment services and crisis services more generally, such as crisis houses and street triage teams. This will enable us to contextualise our findings when establishing the current cost and clinical benefits of PDUs in England as well as modelling the cost and impact of widespread roll out of PDU provision.

#### Synthetic control study

For the synthetic control study, aggregated service use data over the relevant 49 months for both the treated trusts and the selected control trusts will be sourced from Hospital Episodes Statistics (HES) and the Mental Health Services Data Set (MHSDS). The relevant time period is 49 months, as the month following the introduction of the PDU is excluded from the analysis to allow a bedding in time for set-up. HES and MHSDS are databases recording all admissions, outpatient appointments and ED attendances at NHS hospitals in England and mental health NHS trust service use respectively (NHS Digital, [42]).

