### Sample size: ITS

The weekly series for 24 months pre- and post-implementation of PDUs (208 weekly or 48 monthly time points) is more than the 40 data points (20 pre- and 20 post-change) typically considered as adequate for valid ITS model analysis [38], and provides sufficient power to detect medium effects where they exist. For example, to detect a time x slope interaction with medium effect size on an outcome, a sample of 208 time points has > 99% power (assuming one parameter tested and no more than five factors entered in model; calculated using G-Power, ‘linear multiple regression: fixed model, r^2^ increase’ module).

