### Sample size: synthetic control study

The monthly series for 24 months pre- and 24 months post-implementation of PDUs (including a one-month ‘bedding in month’), yields 49 time points. This provides us more than the 40 data points (20 pre- and 20 post-change) typically considered as adequate for valid ITS model analysis [38], and provides sufficient power to detect medium effects where they exist.

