### Data collection

#### Interrupted time series

Outcome data will be collated as time series for 24 months pre- and 24 months post-implementation of the PDU. All data will be aggregated to a single observation at multiple time points at equal intervals. In our case, depending on the variable under study, the time series aggregation unit will be weeks or months. For out of area admissions, for example, a weekly total may be too low to appropriately use a weekly time series as differences may reflect random variation rather than a real effect (i.e. a high noise-signal ratio). The aggregation unit used will be the one that provides proportionately better model fits. Aggregated service use data over the relevant 4 years will be sourced locally from mental health trusts and the ED (acute hospital trusts) of participating PDU sites, as detailed above, through contact with Information Management & Technology (IM&T) departments at each trust. Where a substantial proportion of PDU patients (≥ 25%) are referred from a second acute trust, we will use data from that trust also. All data is handled in accordance with the UK Data Protection Act 2018 (incorporating the EU20 General Data Protection Regulation). Information Management Services personnel within the NHS Trusts will collate the trustwide service use data required for study analyses. Electronic transfer of this data between NHS Trusts and the lead university (St George’s, University of London [SGUL]) will be by encrypted email transfer. This data does not include personally identifiable information and will not be shared by SGUL with any third party or linked with other data that might render the information more identifiable. All data held on NHS or university computers will be securely held on password protected servers and not on individual PCs. The datasets generated during and/or analysed during the current study will be stored in a non-publicly available repository.

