For outcomes relying on count data (e.g., rate of inpatient admissions per 1000 trust catchment population), a generalized linear model for a Poisson distribution (or negative binomial model where count data is overdispersed) using a segmented approach will be fitted [34]. For each outcome, we will calculate regression coefficients corresponding to both change in level (outcome) and trend (slope) after the introduction of PDUs. In this model, the estimated parameters of interest are as follows: 1. the underlying trend prior to PDU introduction (b1); 2. the level change immediately following PDU introduction (b2); 3. the slope change from pre- to post-PDU introduction (using the interaction between time and change; b3); 4. the trend (slope change) following PDU introduction (b1_b3). External validity will be explored by examination of primary outcomes in subgroups, including, for example, gender. Graphical analysis will help to identify any stepwise change in outcome measures as a result of the introduction of PDUs and detect changes in activity patterns before and after the introduction of PDUs. We will conduct separate segmented regression analyses at each PDU site to provides individual estimates (and allow for evaluation of PDU implementation at a local level). Subsequently, to estimate overall effects, individual estimates of intervention effect will be pooled across sites (using inverse variance weights in a meta-analytical model to account for heterogeneity [49];).

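### The synthetic control drops the first month after opening as bedding-in, but the ITS of the same trusts keeps it, where it can bias the level and slope changes

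*Protocol article*

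**What the plan says.** **Synthetic control.** Under Data collection, the article states that "the month following the introduction of the PDU is excluded from the analysis to allow a bedding in time for set-up". The matching sample size section counts the window as 24 months before and 24 after, "including a one-month ‘bedding in month’), yields 49 time points".

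**ITS.** The ITS sample size section gives "The weekly series for 24 months pre- and post-implementation of PDUs (208 weekly or 48 monthly time points". The data collection section agrees: "Outcome data will be collated as time series for 24 months pre- and 24 months post-implementation of the PDU". It adds "Aggregated service use data over the relevant 4 years will be sourced locally". Neither section mentions a bedding-in period.

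**ITS parameters.** The analytical strategy lists, among the parameters of interest, "the level change immediately following PDU introduction (b2" and "the slope change from pre- to post-PDU introduction (using the interaction between time and change; b3". Site estimates are then pooled with inverse variance weights.

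**Shared outcome.** Table 2 makes the rate of psychiatric ED presentations a primary outcome of both studies. The admissions primary outcome differs: all admissions for the synthetic control, informal admissions for the ITS.

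**The concern.** Bedding-in is a property of the unit, not of the data source or the model. If the first month is too unrepresentative to use in the synthetic control, the same reasoning applies to the ITS of the same units, and the article gives no reason for treating them differently.

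The difference falls on the quantities that the ITS reports. The first post-opening points lie at the end of the post segment that determines b2, and they also pull on b3. A unit that works only partly in its first month would make the level change look smaller and would add an upward drift in effect that is not real. These estimates go into the pooled result. The synthetic control, which is meant to support the ITS, would not carry this distortion.

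**Working it through.** **1. The plan's own counts.**
- ITS: 24 × 52/12 × 2 = 208 weeks, or 24 + 24 = 48 months. Both reproduce.
- Synthetic control: 24 + 1 + 24 = 49 months collected, 48 analysed.
- Numbering months from opening, the ITS post period is months 1-24 and the synthetic control post period is months 2-25. They share months 2-24, that is 23 of 24.
- ITS power at 208 points, by noncentral F with one tested parameter and five predictors: 0.9998, in line with the stated value above 99%. The article gives neither alpha nor a numerical effect size, so two-sided 0.05 and f² = 0.15 are assumed.

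**2. Model for the check.** Linear segmented regression (intercept, time, post indicator, time since opening), fitted by least squares to a noise-free series. The true effect is a constant D, except in the first month (monthly series) or first four weeks (weekly series). The article gives no set-up behaviour, so two cases are assumed:
- wholly absent: zero effect in that month;
- half absent: half the effect in the monthly series, or a linear ramp of 1/5, 2/5, 3/5, 4/5 over four weeks in the weekly series.

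The pre segment is fitted exactly, so only the post line matters. With n post points at k = 0, …, n−1, mean k̄ and Sxx = n(n²−1)/12, a point at k has
- weight 1/n + k̄(k̄−k)/Sxx on b2;
- weight (k−k̄)/Sxx on b3.

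**3. Monthly (n = 24, k̄ = 11.5, Sxx = 1150), wholly absent.**
- Weight of month 1 on b2: 1/24 + 11.5²/1150 = 0.0417 + 0.1150 = 0.157. So b2 = 0.843D.
- b3 = 11.5/1150 = 0.010D per month; × 24 = 0.24D.
- Mean post-period effect: 23/24 = 0.958D.

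Half absent: b2 = 0.922D, slope change 0.005 × 24 = 0.12D, mean 0.979D.

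**4. Weekly (n = 104, k̄ = 51.5, Sxx = 93,730), wholly absent for four weeks.**
- Combined weight on b2: 4/104 + 51.5 × (51.5 + 50.5 + 49.5 + 48.5)/93,730 = 0.0385 + 0.1099 = 0.148. So b2 = 0.852D.
- b3 = 200/93,730 = 0.00213D per week; × 104 = 0.22D.
- Mean: 100/104 = 0.962D.

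Linear ramp: b2 = 0.925D, slope change 0.00108 × 104 = 0.11D, mean 0.981D.

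| Series | First-month effect | b2 | False slope change over 24 months | Mean post effect |
|---|---|---|---|---|
| Monthly | none | 0.84D | 0.24D | 0.96D |
| Monthly | half | 0.92D | 0.12D | 0.98D |
| Weekly | none | 0.85D | 0.22D | 0.96D |
| Weekly | ramp | 0.93D | 0.11D | 0.98D |

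**5. With the month dropped and the series extended by one month.** b2 = D and b3 = 0 in both series. The standard error of b2 at opening, in residual SDs with independent errors, goes
- monthly from 0.578 to 0.596 (0.596/0.578 = 1.03);
- weekly from 0.2774 to 0.2855 (ratio 1.03).

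**6. With the month dropped and no extension.**
- Monthly, 23 post points at k = 1, …, 23: the post part of the variance is 1/23 + 12²/1012 = 0.186 and the pre part is 1/24 + 12.5²/1150 = 0.178. The standard error is √0.363 = 0.603, a ratio of 1.04.
- Weekly, 204 points: the power calculation of step 1 still gives 0.9998.

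**The case against.** **The text is silent rather than contradictory, and a condensed article may leave transition handling to the full protocol or SAP.** This has some force. The four-year wording is loose: the Discussion also calls the synthetic control window four years although it is 49 months. The point counts are firmer. The article adds the bedding-in month explicitly for one study and gives 208 or 48 points for the other without it. It therefore states two windows, and the natural reading is that the ITS has no exclusion.

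**Keeping the opening month is a legitimate choice.** The ITS explicitly targets the change on introduction. That is a fair reason to report the version with the month kept, but the article does not offer it as the reason for the difference.

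**The bias is small beside the sampling error.** With D equal to one residual SD and the effect wholly absent, the bias in b2 is 0.157/0.578 = 0.27 standard errors monthly and 0.148/0.277 = 0.53 weekly. The mean post-period effect hardly moves. This stands, and it limits the weight of the point.

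**Stronger readings that the documents do not support.** A reader might infer that any disagreement between the two analyses would come from the window. They also differ in data source (local extracts against national datasets), control group, risk adjustment and estimand, and one of the two primary outcomes is not the same. A reader might also infer that b2 is estimated from the set-up month alone. It is fitted from all points, and that month carries about 15-16% of the post-segment weight.

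The planned sensitivity analyses do not cover the gap. They address other service changes, the number of control trusts and the number of pre-intervention periods, not the unit's own set-up.

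**Conclusion.** The point holds as a bedding-in rule applied to one of two linked analyses without a stated reason. If the effect is half to wholly absent in the first month and constant afterwards, the ITS level change is attenuated by about 7-16% and a false slope change of about 0.11-0.24D over 24 months appears. The mean post-period effect is diluted by only about 2-4%.

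These sizes rest on assumed set-up behaviour and on a linear model. The bias figures come from an unweighted least-squares fit, and the standard errors assume independent errors. The Poisson or negative binomial fits, and any autoregressive terms, would change the figures somewhat. The upper end is a worst case within the range examined, not an established bias. The window is one avoidable source of disagreement between the ITS and the synthetic control, alongside the others named above. The change is worth making because it is cheap and follows the plan's own reasoning.

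**What to change.** Apply the same exclusion to the ITS: treat the first month after opening (about four weeks in a weekly series) as a transition period and leave it out of the primary fit. Preferably collect 49 months so that 24 post months remain; otherwise accept 23. State whether b2 refers to the opening date or to the first month after bedding-in. Report the ITS with the month included as a sensitivity analysis.

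The cost is one more month of local aggregate data per site, a few lines in the protocol or SAP, and a standard error for b2 about 3% larger with the extension (about 4% monthly without it). The synthetic control already needs month 25 for the same trusts, so the extension asks for no calendar month that the study does not already plan to cover.

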#### Key informant interviews

Semi-structured interviews (*n* = 5 per site) will be held with strategic managers in each site, including PDU manager, Acute Care Pathway lead, mental health lead commissioner (or their equivalent locally) and the ED manager and ED clinical director at the main general hospital at each site. Interviews will seek to identify any changes to the crisis care pathway within the duration of the time series, including the introduction or withdrawal of services or new initiatives, including provision of services outside of the NHS mental health trust (e.g. by third sector agencies), changes in policy or protocol relating to the assessment and managing of psychiatric presentation to ED and seasonal impacts.

To account for potential confounding of any identified service reconfiguration or changes to models of care, sensitivity analysis comparing the months following the introduction of PDUs to the same period prior to the service change will be administered. These data will be used in interpreting time series curves for each of our outcomes (for example, where reconfiguration of community services was followed by a temporary spike in inpatient admissions, or where the introduction of a street triage service coincided with a sustained reduction in ED presentation).

## Analytical strategy

### Interrupted time series

We will use segmented regression analysis of interrupted time series data [34, 43] for the ITS. This approach minimizes threats to internal validity while maximizing external validity by taking into account any serial correlation, background variation and underlying trends independent of the intervention over time. Segmented regression analysis is the most common method used in ITS of healthcare interventions [44] and has previously been successfully used to predict emergency department (ED) presentations and hospital admission [45, 46], including psychiatric admissions and mental health-related ED visits [47].

Initially, for each outcome, to check for serial auto-correlation due to repeated measures, we will examine the plot of residuals from regression analyses and use the Durbin-Watson test [48]. Where no significant autocorrelation is detected, we will use a simple time series regression model. If significant autocorrelation exists, we will investigate several autocorrelation structures and adjust for effects as required. For example, where correlations due to seasonal associations are observed, monthly or seasonal dummy variables will be introduced in the model. Where weekly/monthly observations are not independent of one another, we will include a correlation structure based on the most appropriate autoregressive and moving average terms (assessed using plots of autocorrelation and partial correlation). Akaike’s and Schwarz’s Bayesian information criteria will be used to select most appropriate models.

For outcomes relying on count data (e.g., rate of inpatient admissions per 1000 trust catchment population), a generalized linear model for a Poisson distribution (or negative binomial model where count data is overdispersed) using a segmented approach will be fitted [34]. For each outcome, we will calculate regression coefficients corresponding to both change in level (outcome) and trend (slope) after the introduction of PDUs. In this model, the estimated parameters of interest are as follows: 1. the underlying trend prior to PDU introduction (b1); 2. the level change immediately following PDU introduction (b2); 3. the slope change from pre- to post-PDU introduction (using the interaction between time and change; b3); 4. the trend (slope change) following PDU introduction (b1_b3). External validity will be explored by examination of primary outcomes in subgroups, including, for example, gender. Graphical analysis will help to identify any stepwise change in outcome measures as a result of the introduction of PDUs and detect changes in activity patterns before and after the introduction of PDUs. We will conduct separate segmented regression analyses at each PDU site to provides individual estimates (and allow for evaluation of PDU implementation at a local level). Subsequently, to estimate overall effects, individual estimates of intervention effect will be pooled across sites (using inverse variance weights in a meta-analytical model to account for heterogeneity [49];).

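### Making seasonal terms conditional on a significant Durbin-Watson test can leave an annual cycle in the model and create a false level change (b2) in the interrupted time series

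*Protocol article*

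**What the plan says.** The rule is in the protocol article, Analytical strategy, Interrupted time series. For each outcome the analyst inspects a residual plot and runs the Durbin-Watson test. Then: "Where no significant autocorrelation is detected, we will use a simple time series regression model". The next sentence covers the opposite result, significant autocorrelation, and gives as an example that "where correlations due to seasonal associations are observed, monthly or seasonal dummy variables will be introduced in the model". Autoregressive and moving-average terms follow in the same place, and information criteria (AIC and BIC) close the paragraph.

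The parameters of interest include "the level change immediately following PDU introduction (b2") and the slope change b3, estimated for every outcome at each site and then pooled by inverse variance. Series length comes from Sample size: ITS, "The weekly series for 24 months pre- and post-implementation of PDUs (208 weekly or 48 monthly time points"). Under Data collection, "the time series aggregation unit will be weeks or months", depending on the variable, so 48-point series can occur.

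The Discussion repeats that autocorrelation will be controlled only if indicated. Study design, however, counts control of periodicity among the advantages of the method, and the key informant interviews ask about seasonal effects. The authors expect seasonality, but the written rule does not guarantee that it is modelled.

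**The concern.** An annual cycle is a feature of the mean, whereas Durbin-Watson asks whether neighbouring residuals are correlated. A moderate cycle spread over twelve months or 52 weeks gives only weak lag-1 correlation, so a non-significant result says little about the season. The test was also built for linear regression, while the rate outcomes, including both ITS primaries, are to be fitted by Poisson or negative binomial models.

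It is natural to think that two whole years on each side make the cycle cancel. They do so for the segment means but not for the fitted lines. Within a segment the cycle correlates with time and tilts the line. Both segments tilt equally, so the slope change is untouched, but at the join the tilts produce a step. That step is b2, which would be read as the immediate effect of opening the unit.

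**Working it through.** **Inputs.** From the article: 24 months each side, 48 monthly or 208 weekly points; four-term segmented model; Durbin-Watson first. Not in the article, so assumed: amplitude A of an annual sinusoid, opening month (phase), AR(1) correlation rho, 5% level, Gaussian errors, one-sided Durbin-Watson with critical values simulated for this design.

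**The plan's own figure.** The article states that "a sample of 208 time points has > 99% power (assuming one parameter tested and no more than five factors entered in model"). Taking medium as f² = 0.15 (assumed), λ = 0.15 × 208 = 31.2 with 1 and 202 degrees of freedom gives power 0.9998, so the figure reproduces. With 48 points, λ = 7.2 and power is 0.746. The stated power concerns the slope interaction and does not bear on bias in b2.

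**Bias in b2 from an omitted cycle.** With m points per segment and a period of P points that divides m, the largest fitted tilt per unit amplitude is [m / (2 sin(π/P))] / [m(m² − 1)/12]. The two lines then differ at the join by m times that tilt.
- Monthly (m = 24, P = 12): 24 / (2 × 0.2588) = 46.4; 24 × 575 / 12 = 1150; tilt 0.0403; step 24 × 0.0403 = **0.97A**.
- Weekly (m = 104, P = 52): 104 / (2 × 0.06038) = 861; 104 × 10,815 / 12 = 93,730; tilt 0.00919; step 104 × 0.00919 = **0.96A**.
- The step varies sinusoidally with opening date, so its root mean square is 0.97A / √2 = **0.68A**, and it is near zero at the most favourable date.
- The bias in b3 is zero at every phase.

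For scale, if a series varied by ±5% over the year, the false step could reach 0.97 × 5% = 4.9%.

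**How often the test misses it.** Simulation with no true effect and A = 0.5 residual SD; the test-first rule adds one annual sine/cosine pair only if Durbin-Watson is significant.

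| | Monthly (48) | Weekly (208) |
|---|---|---|
| Durbin-Watson detects the cycle | about 18% | about 42% |
| False positives for b2, averaged over opening dates | about 7% | about 14% |
| Same, worst opening date | about 10% | about 23% |
| Sine/cosine pair always in the model | 5% | 5% |

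For monthly series on a grid of twelve phases (largest bias 0.93A), amplitudes of 0.5, 0.75 and 1.0 SD leave a mean bias in b2 of 0.35, 0.38 and 0.27 SD under the test-first rule, with false-positive rates of 9.9%, 12.0% and 11.5%.

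**Cost of always adjusting.** At 48 points the standard error of b2 goes from 0.575 to 0.613 SD with one harmonic pair (0.613 / 0.575 = 1.07) and to 0.641 SD with eleven month dummies (+11%).

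**Serial correlation (secondary).** At 48 points and rho 0.2, 0.3, 0.4, Durbin-Watson detects 34%, 56% and 77%. The false-positive rate for b2 is 7.8%, 9.5% and 8.7% when AR(1) errors are fitted only after a significant test, and 6.2%, 7.4% and 7.0% when AR(1) by REML is always fitted.

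**The case against.** The strongest reply is that the simulation isolates Durbin-Watson, while the article offers more: a residual plot, autocorrelation and partial autocorrelation plots, and AIC/BIC. If AIC chose between no season and one harmonic pair for every series, then at A = 0.5 SD and the worst phase it would pick the season in 99.9% of weekly and 73% of monthly series, with false-positive rates for b2 of 4.7% and 7.1%. This stands as mitigation. It does not settle the matter, because the written order sends a non-significant series to the simple model before those steps, and BIC penalises each extra term more heavily than AIC (ln 48 = 3.9 against 2).

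The weekly and monthly columns are also not like for like: 0.5 weekly SD is roughly 0.5 × √(52/12) = 1.04 monthly SD under independent errors. Pooling sites with different opening months would partly offset the biases, but the article gives no opening months. The synthetic control study cross-checks the emergency department primary; it does not correct b2, and its admissions primary counts all admissions rather than informal ones.

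An article may leave model detail to a fuller plan. Here, though, the objection is to a rule the article states.

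Three stronger readings are tempting:
- *That b2 is wrong in 10% of monthly and nearly 40% of weekly series.* Rates near 10.5% and 38% apply only to series the test has missed and only at the worst opening date.
- *That the standard errors are seriously too small.* That arises from undetected positive autocorrelation, not from the cycle, and in weekly series the test detects rho 0.2 in 88% and 0.3 in 99%. In monthly series, always fitting AR(1) gains only about two percentage points.
- *That Newey-West errors should therefore be used throughout.* At 48 points with lag 3 they give about 12 to 14% false positives with no autocorrelation and 15 to 19% at rho 0.2 to 0.4, worse than the rule they would replace.

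**Conclusion.** The concern holds for seasonality. As written, the rule can leave an annual cycle in the model, and the level change then absorbs up to about 0.97 of its amplitude, with a root mean square of about 0.68 over opening dates. The slope change is not affected. That bias is exact for a sinusoid and this design.

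The error rates are conditional. They assume A = 0.5 residual SD, Gaussian errors and Durbin-Watson acting alone: about 7% monthly and 14% weekly on average, 10% and 23% at the worst opening date, against 5% with the season always modelled. With no cycle and no autocorrelation the rule keeps 5%. The article gives neither amplitude, rho nor opening months, so it does not show that any particular estimate will be biased. The matter merits a wording change before analysis and does not undermine the ITS design. The serial-correlation part is a modest secondary point.

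**What to change.** State that every ITS model contains seasonal terms whatever the Durbin-Watson result: one annual sine/cosine pair, or calendar-month terms for weekly data. Keep Durbin-Watson and the autocorrelation plots as diagnostics for correlation that remains after seasonal adjustment.

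As a secondary change, fit AR(1) errors by REML in every linear model rather than only after a significant test. This lowers the error rate at 48 points but does not bring it fully to 5%. Do not prescribe Newey-West errors for the 48-point series.

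The cost is a sentence or two of analysis wording and about 7% in the standard error of b2 when there is in fact no season. No extra data are needed.
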